**Methods:**

This is an open-label, multicenter, 1:1 cluster-randomized trial of LPV/r 800/200 mg twice daily for 14 days (intervention arm) versus no intervention (control arm), using an adaptive approach to sample size calculation. Participants will be individuals aged > 6 months with a high-risk exposure to a confirmed COVID-19 case within the past 7 days. A combination of remote and in-person study visits at days 1, 7, 14, 35, and 90 includes comprehensive epidemiological, clinical, microbiologic, and serologic sampling. The primary outcome is microbiologically confirmed COVID-19 infection within 14 days after exposure, defined as a positive respiratory tract specimen for SARS-CoV-2 by polymerase chain reaction. Secondary outcomes include safety, symptomatic COVID-19, seropositivity, hospitalization, respiratory failure requiring ventilator support, mortality, psychological impact, and health-related quality of life. Additional analyses will examine the impact of LPV/r on these outcomes in the subset of participants who test positive for SARS-CoV-2 at baseline. To detect a relative risk reduction of 40% with 80% power at *α* = 0.05, assuming the secondary attack rate in ring members (*p*_0_) = 15%, 5 contacts per case and intra-class correlation coefficient (ICC) = 0.05, we require 110 clusters per arm, or 220 clusters overall and approximately 1220 enrollees after accounting for 10% loss-to-follow-up. We will modify the sample size target after 60 clusters, based on preliminary estimates of *p*_0_, ICC, and cluster size and consider switching to an alternative drug after interim analyses and as new data emerges. The primary analysis will be a generalized linear mixed model with logit link to estimate the effect of LPV/r on the probability of infection. Participants who test positive at baseline will be excluded from the primary analysis but will be maintained for additional analyses to examine the impact of LPV/r on early treatment.

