^d^An additional swab is to be collected within 24 h if symptoms develop before day 14. Two respiratory specimens (swabs, saliva, etc.) are to be taken at day 14 timepoint, unless an extra swab was already taken due to the development of symptoms in which case only one is collected

*NB:* other respiratory specimen(s) may be collected depending on availability of supplies

^e^The dried blood spot at baseline is to be performed in participants in the active arm only (since these participants are already collecting a drop of blood for the HIV self-test), for SARS-CoV-2 serology

^f^The dried blood spot at day 14 is to be performed in a random subsample of participants in the active arm only, for lopinavir levels. These participants are the only ones that require a CBC at day 35 since the hematocrit is required for interpretation of DBS lopinavir levels [42, 43]

^g^Baseline serology is to be collected at baseline only if the participant is institutionalized

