### Sample size {14}

Our target sample size is 244 rings, assuming an average ring size of 5 individuals (i.e., a total of *n* = 1220 participants), an intra-class correlation coefficient (ICC) of 0.05 [31], a secondary attack rate (proportion of those exposed who get infected, p_0_) of 15%, and inflation for 10% loss-to-follow-up. This sample size will allow us to detect whether the study drug decreases the relative risk of COVID-19 by at least 40% (effect size estimated in the MERS-CoV LPV/r PEP study [8]), with 80% power and alpha = 0.05.

The number of contacts per case may vary considerably but was estimated at 5 based on published data for SARS in Beijing (mean = 3.8) [49]. We considered ICC values of 0.02 and 0.05 [31]. The estimated secondary attack rate of 15% was originally estimated based on transmission rates for SARS [49–52] and influenza [53–56] and is corroborated by recent studies on COVID-19. Among 19 household contacts of the first 10 patients with travel-related COVID-19 in the United States, *p*_0_ = 10.5% (95%CI = 2.9%–31.4%) [57]. In Shenzhen, the secondary attack rate among 686 household contacts was 11.2% (95%CI = 9.1–13.8) [58]. In Guangzhou, it was 19.3% (95%CI = 15.5–23.9%) among household contacts sharing a residential address with a case [59]. Investigators in Wuhan found secondary transmission in 64/392 household contacts (16.3%) [60]. Illness compatible with COVID-19 developed in 58/407 (14.8%) of placebo arm participants in a recent trial of hydroxychloroquine as COVID-19 PEP [61].

The parameters *p*_0_, ICC and cluster size are important drivers of statistical power [62, 63], but are still being elucidated for COVID-19 and may vary according to context. We will thus apply an adaptive trial design [63] to revise our sample size calculations based on day 14 data from the first 60 clusters.

Another interim analysis will be done when day 14 data for 50% of the target sample have accrued; our independent data safety monitoring committee will advise on trial continuation/switching to a different agent, taking external data into account, and through additional confidential consultation with the WHO Core DSMC on COVID-19 prophylaxis, with which we are linked [5].

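### The 80% power at 244 rings makes no allowance for unequal ring sizes, although the plan expects ring size to vary; the loss is under 1 to about 7 points at ICC 0.05, depending on an assumed CV

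*Protocol article*

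**What the plan says.** Sample size {14} sets the target: "Our target sample size is 244 rings, assuming an average ring size of 5 individuals", with ICC 0.05, a control attack rate of 15%, a 40% relative reduction and 10% loss to follow-up, "with 80% power and alpha = 0.05". The Methods paragraph of the abstract gives the step before inflation: "we require 110 clusters per arm, or 220 clusters overall and approximately 1220 enrollees after accounting for 10% loss-to-follow-up".

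On ring size, Sample size {14} says: "The number of contacts per case may vary considerably but was estimated at 5". It gives no standard deviation, CV or variance-inflation term. It also reports that ICC values of 0.02 and 0.05 were considered.

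The same section treats attack rate, ICC and cluster size as uncertain and plans to revise the sample size on day 14 data from the first 60 rings. The abstract lists the same three inputs. Neither place prints the formula for the revision or says whether cluster size means the mean only or also the spread.

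**The concern.** When ring sizes differ, the design effect at a given mean is larger than when all rings are equal, because large rings contribute correlated observations with diminishing information. A calculation that uses only the mean therefore overstates power. Here the section that uses the mean also says that the number of contacts is expected to vary.

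This is a separate matter from whether the mean itself is 5. Even if the mean, the ICC, the attack rate and the effect are all right, the power of the primary comparison would fall short of the stated figure once the spread is more than mild. The stake is a modest loss of power, and the chance that the 60-ring revision repeats the simplification.

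**Working it through.** **Inputs from the article.** Control 15%; intervention 15% × (1 − 0.40) = 9%; alpha 0.05, taken as two-sided because that reproduces the figure; power 80%; ICC 0.05; mean ring size 5; 10% loss; 244 rings, so 122 per arm.

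**Input not in the article.** The CV of ring size. I assume 0.3 to 1.0, that is, an SD of 1.5 to 5 contacts around a mean of 5.

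**Step 1: reproduce the plan.** With pooled variance, n per arm = [1.96 × √(2 × 0.12 × 0.88) + 0.8416 × √(0.15 × 0.85 + 0.09 × 0.91)]² / 0.06² = (0.9008 + 0.3851)² / 0.0036 = 459.
- Equal-size design effect: 1 + (5 − 1) × 0.05 = 1.20.
- Rings per arm: 459 × 1.20 / 5 = 110.2, against 110 stated.
- After loss: 220 / 0.9 = 244 rings, and 1100 / 0.9 = 1222 people, against about 1220 stated.

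The figure reproduces with zero variation in ring size.

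**Step 2: allow for unequal rings.** Design effect DE = 1 + [(1 + CV²) × m − 1] × ICC. If the 10% loss is of individuals, m = 4.5 and each arm has 122 × 4.5 = 549 people. Effective n = 549 / DE, and power = Φ[(0.06 × √(effective n) − 0.9008) / 0.4576]. Rings needed in total = 2 × 459 × DE / 4.5.

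Example, CV 0.7: DE = 1 + (1.49 × 4.5 − 1) × 0.05 = 1.285; effective n = 427; power = Φ[(0.06 × 20.67 − 0.9008) / 0.4576] = Φ(0.74) = 77.1%.

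| CV | DE (m = 4.5) | Power, individuals lost | Power, whole rings lost (110 × 5 per arm) | Rings for 80% (individuals lost) |
|---|---|---|---|---|
| 0 | 1.175 | 80.7% | 79.9% | 240 |
| 0.3 | 1.195 | 80.0% | 79.2% | 244 |
| 0.5 | 1.231 | 78.8% | 77.9% | 251 |
| 0.7 | 1.285 | 77.1% | 76.0% | 262 |
| 0.9 | 1.357 | 74.8% | 73.5% | 277 |
| 1.0 | 1.400 | 73.5% | 72.1% | 286 |

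**Step 3: ICC 0.02.** With individual loss, power is 84.2% at CV 0, 82.7% at CV 0.7 and 81.2% at CV 1.0. With whole-ring loss it is still 80.6% at CV 1.0.

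**Step 4: is the formula too harsh for a mixed model?** The primary analysis is a GLMM, which weights rings more efficiently. The relative-efficiency version, with λ = m × ICC / (m × ICC + 1 − ICC) and efficiency 1 − CV² × λ(1 − λ), gives 79.1% at CV 0.5, 77.5% at CV 0.7, 75.2% at CV 0.9 and 73.8% at CV 1.0, with individual loss. A beta-binomial simulation with optimal weights (122 rings per arm, 10% individual loss, 4000 runs) gave 80.7% at CV 0, 80.1% at 0.4, 78.7% at 0.6, 78.1% at 0.8 and 75.1% at 1.0. The direction is the same and the loss slightly smaller.

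**The case against.** The strongest reply is that nothing is miscalculated. The 110 reproduces, the power is stated on the assumption of an average ring of 5, and the plan itself calls cluster size uncertain and commits to a revision after 60 rings. The exact design-effect term could also stand in the full protocol or SAP, which are not shown. This largely stands: the point is a planning simplification that conflicts with the plan's own expectation, not an arithmetic slip.

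Three stronger readings are tempting, and the documents do not support them.

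- A reader might infer that 80% power holds only if every ring is exactly the same size. It does not: with individual-level loss, power is still 80.0% at CV 0.3, and at ICC 0.02 it stays above 80% up to CV 1.0.
- A reader might infer that the revision will carry the shortfall forward. No revision formula is printed, so this is a risk and not a fact. Nothing shown, however, brings the spread of ring size into either the initial or the revised calculation.
- A reader might infer a few very large institutional rings from the note to the schedule table, "Baseline serology is to be collected at baseline only if the participant is institutionalized". That note only governs when serology is drawn. Study setting {9} describes community-based participants, healthcare workers appear as a subgroup because attack rates differ, and super-spreading is raised to explain the unit of randomization. None of these gives a ring size, and choosing the index case as the unit does not by itself put ring-size variance into the sample size.

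**Conclusion.** The point holds in limited form. The stated 80% is the power under equal ring sizes, while the same section expects variation.

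At the design ICC of 0.05, 244 rings give about 80% power at CV 0.3, 79% at 0.5, 77–78% at 0.7, 75% at 0.9 and 74% at 1.0 if individuals are lost, and about 1 point less if whole rings are lost. Restoring 80% on the individual-loss basis would take about 251 rings (CV 0.5) to 286 (CV 1.0).

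The size rests entirely on the assumed CV, which the documents neither give nor exclude, and on ICC 0.05 being right. Since 244 is a provisional target, the shortfall would remain in the final design only if the 60-ring revision again used the mean alone.

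**What to change.** 1. In the abstract's Methods paragraph and in Sample size {14}, say that 80% power assumes equal ring sizes. Give the power at 244 rings for a stated range of assumed CVs, all by one formula and one convention for loss (individuals or whole rings), for example the individual-loss column above.

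2. State that the revision after 60 rings uses 1 + [(1 + CV²) × m − 1] × ICC, or the slightly less conservative relative-efficiency version suited to the mixed model. The mean and CV of ring size should be those observed in the same rings, pooled over arms.

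The cost is wording and one extra term. Implementation {16c} has every member's decision on participation recorded before a ring is randomized, so ring sizes are available and a CV pooled over arms needs no unblinding. The downside is that the stated power becomes slightly less favourable and, if the observed spread is large, the revised target may rise.

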### Recruitment {15}

Enrollment of exposed persons will typically occur by first identifying new lab-confirmed COVID-19 cases, and then conducting contact tracing to define a ring of exposed contacts around those index cases. The study team will actively seek out such new cases by building referral pathways from COVID-19 Assessment Centres, Emergency Departments, inpatient units, occupational health departments, and public health authorities in the vicinity of each study site. Once the list of exposed contacts for each case is identified, the study team will make multiple attempts to contact them for up to 24 h, in order to obtain their decision about trial participation.

In addition, the team will post advertisements on social media seeking both individuals who have been newly diagnosed, as well as people who have recently been exposed to a confirmed case. As the epidemic evolves, the study team will consider expansion of the trial to other study sites in jurisdictions with increasing numbers of cases.

## Assignment of interventions: allocation

### Sequence generation {16a}

Rings will be randomized to the intervention or control conditions in a 1:1 ratio in permuted blocks of variable size and stratified by study site, according to a computer-generated sequence of random numbers. Block sizes will not be revealed to study staff.

### Concealment mechanism {16b}

Randomization will be implemented using a secure interactive web-based response system (Research Electronic Data Capture, REDCap). To ensure allocation concealment, the randomization sequence is fully concealed, and treatment assignment will not be revealed until the moment of randomization. Study personnel will then notify participants about their assigned study arm at the time of the baseline visit.

### Implementation {16c}

The allocation sequence was generated by a statistician not otherwise involved in the trial, using a computer-generated sequence of random numbers. That statistician is the only person who will have access to the study codes. When interim analyses are conducted, only the codes related to the participants to be included in the interim analysis will be released to the biostatistician from the Data Safety and Monitoring Committee.

Study coordinators will use the web-based system to randomize rings of participants. An automated audit trail will record the time, date, allocation, and participant identification numbers. Each ring will only be randomized once all members of a ring either: give preliminary consent, decline or are classified as not contactable within the 24 h window for obtaining consent. It is essential to secure preliminary consent of the individual participants in a ring before randomization of the cluster in order to avoid selection bias, since this study is open-label.

## Assignment of interventions: blinding

### Who will be blinded {17a}

This trial is open-label at the level of the participant, study coordinator, and investigator due to the impracticality of securing a supply of placebo. However the primary outcome is an objective biological event (microbiologic evidence of virus by RT-PCR), and lab technologists and statisticians will be blinded through the use of a randomly generated secondary participant identification number that is unlinked to cluster.

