### Confidentiality {27}

Participants will be identified using two unique study identification numbers only, and no identifying data will be stored in the central study database. No identifying information will be shared beyond the immediate members of the research team at the study site where the participant is enrolled. Participating sites are responsible for keeping any identifiable information in locked locations, if in hard copy, or in password-protected files on secure servers, if in soft copy.

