## Statistical methods

### Statistical methods for primary and secondary outcomes {20a}

The primary outcome is microbiologically confirmed SARS-CoV-2 infection, i.e., detection of viral RNA in a respiratory specimen (oropharyngeal/nasal swab, nasopharyngeal swab, sputum specimen, saliva specimen, oral swab, endotracheal aspirate, bronchoalveolar lavage specimen) by day 14. Our primary analysis will be a generalized linear mixed model (GLMM) with logit link to estimate the effect of LPV/r on the probability of infection while accounting for clustering of participants in rings, with stratification by the randomizing site. The primary analysis will be unadjusted; in addition, multivariable models will adjust for key characteristics of both contacts (age, sex, co-morbidity, exposure characteristics such as type, duration, and timing) and index cases (illness severity, concomitant medications, etc.). In particular, we will include sex/gender-based analyses with variables specific to contacts and types of exposures. Participants with specimens positive for SARS-CoV-2 at baseline will be permitted to continue in the trial and follow all study procedures, including completion of the 14-day course of study drug for those in the active arm, as noted in section 12.2.2. These participants will be excluded from the primary and secondary analyses regarding LPV/r as PEP, but included in secondary analyses regarding early LPV/r treatment, as noted below.

To assess safety, adverse events will be tabulated according to grade and causality assessment using definitions from the DAIDS Table for Grading the Severity of Adverse Events [28], and compared between study arms.

As for the primary analysis outlined above, GLMM with logit link (for dichotomous outcomes) or identity link (for continuous outcomes) will also be used to compare the following secondary outcomes between study arms:

Symptomatic COVID-19 disease by day 14Seropositivity by day 35Days of hospitalization attributable to COVID-19 disease by day 90Respiratory failure attributable to COVID-19 disease requiring (i) non-invasive and (ii) invasive ventilation by day 90Mortality attributable to COVID-19 diseaseShort-term psychological distress, defined as scoring ≥ 16 on the K10 [45, 46] at day 14Long-term traumatic stress response, defined as scoring ≥ 26 on the IES scale [47, 48] at day 90Health-related quality of life, measured by the EQ-5D-5 L on days 1, 14, 35, and 90

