Additional secondary analyses will examine the role of LPV/r in early treatment of COVID-19, in the subset of participants whose baseline specimens test positive for SARS-CoV-2. GLMM models will be used to compare the same secondary outcome measures described above.

Key transmission-related epidemiologic parameters among exposed contacts including exposure histories, cluster size, secondary attack rate (p_0_, incidence proportion), time to first viral shedding will be analyzed using descriptive statistics. Risk factors for transmission and correlates of symptomatic disease will be analyzed using logistic regression models.

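### The risk-factor models make no stated allowance for rings, and the blinding text needs reconciling with the analyses that require ring membership

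*Protocol article*

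**What the plan says.** **Risk-factor models.** The section on statistical methods for primary and secondary outcomes {20a} specifies a logit mixed model for the primary outcome, "to estimate the effect of LPV/r on the probability of infection while accounting for clustering of participants in rings". Secondary outcomes follow suit: "As for the primary analysis outlined above, GLMM with logit link (for dichotomous outcomes) or identity link (for continuous outcomes) will also be used". The early-treatment comparisons in participants positive at baseline are also assigned mixed models. The next paragraph changes method: "Risk factors for transmission and correlates of symptomatic disease will be analyzed using logistic regression models". No ring term and no clustered variance is mentioned there. These models serve the third secondary objective, which is to characterize transmission among exposed contacts.

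**Blinding.** Section {17a} states that "lab technologists and statisticians will be blinded through the use of a randomly generated secondary participant identification number that is unlinked to cluster". Section {27} adds: "Participants will be identified using two unique study identification numbers only". On release of codes, section {16c} says that at interim analyses "only the codes related to the participants to be included in the interim analysis will be released to the biostatistician" of the data safety and monitoring committee. The Abstract states: "We will modify the sample size target after 60 clusters, based on preliminary estimates of" the control attack rate, the ICC and the cluster size. The sample size section {14} repeats that plan.

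**The concern.** Contacts in a ring are exposed to the same index case, so their outcomes are correlated. The trial design section relies on this when it makes the index case the unit of randomization because of super-spreading. Several natural risk factors, such as the index case's illness severity and medications (both listed in {20a} as adjustment variables), take one value per ring. Ordinary logistic regression treats the contacts in a ring as independent and so overstates the information on such factors. Confidence intervals come out too narrow, and ring-level factors are declared significant too often. Because the preceding analyses all name mixed models, a reader would take the change to logistic regression as deliberate.

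The blinding sentence raises a related difficulty. The primary model and the ICC re-estimate both need to know which participants belong to the same ring, yet the identifier described for statisticians is one that cannot show this. Without clarification, someone must work out during the trial how ring membership reaches the analyst. In an open-label trial that cites blinded statisticians as a safeguard, that should be settled in advance.

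**Working it through.** **Inputs.** From {14} and the Abstract: control attack rate 15%, relative risk reduction 40% (so 9% on drug), power 80%, alpha 0.05, mean ring size m = 5, ICC 0.05 (0.02 also considered), 10% loss to follow-up. Two-sided testing is assumed, since the article does not state sidedness. An ICC of 0.10 is assumed as an upper value; {14} itself says the ICC is still uncertain.

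**Step 1: reproduce the plan's figure.** For two proportions with pooled variance under the null, the number per arm is

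[1.96·√(2·0.12·0.88) + 0.8416·√(0.15·0.85 + 0.09·0.91)]² / 0.06² ≈ 459.3, rounded up to 460.

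The design effect is 1 + (5 − 1)·0.05 = 1.20. Then 460 × 1.20 = 552, and 552 / 5 = 110.4 clusters per arm, against 110 stated. Allowing for loss, 1100 / 0.9 = 1222, against about 1220 stated. The plan's own clustering assumptions are therefore understood correctly.

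**Step 2: ignore rings for a factor constant within rings.** The correct standard error is √DE times the ordinary one, with DE = 1 + (m − 1)·ICC. The ordinary one is too small by 1 − 1/√DE, and a nominal 5% test has true size 2·[1 − Φ(1.96/√DE)].

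| ICC | DE (m = 5) | √DE | SE too small by | True size |
|---|---|---|---|---|
| 0.02 | 1.08 | 1.039 | 3.8% | 5.9% |
| 0.05 | 1.20 | 1.095 | 8.7% | 7.4% |
| 0.10 (assumed) | 1.40 | 1.183 | 15.5% | 9.8% |

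**Step 3: which factors are affected.** Logistic regression was simulated with 220 rings of 5, 15% risk, beta-binomial ICC 0.05, a factor with no effect, and 2000 replicates per row. The Monte Carlo error on a 5% rate is √(0.05·0.95/2000), about 0.5 percentage points.

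| Within-ring correlation of the factor | True SE / ordinary SE | Size, ordinary | Size, cluster-robust |
|---|---|---|---|
| 1 (ring-level) | 1.10 | 7.7% | 5.7% |
| 0.5 | 1.06 | 7.2% | 6.4% |
| 0.25 | 1.01 | 5.5% | 4.9% |
| 0 (unrelated to ring) | 0.98 | 4.5% | 4.9% |
| Purely within ring | 0.98 | 4.2% | 4.9% |

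The first row agrees with the formula. Inflation fades as the factor varies more within rings. For factors unrelated to ring, the ordinary standard error is about right or slightly large.

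**Step 4: unequal rings.** Section {14} expects the number of contacts per case to vary considerably but gives no distribution. As an illustration, assume geometric ring sizes with mean 5, so the variance is 20 and CV² = 20/25 = 0.8. Then DE = 1 + [(1 + 0.8)·5 − 1]·0.05 = 1.40 at ICC 0.05, and the true size is 9.8%. A simulation with 244 rings, 12% risk and these sizes gave 9.7%, against 7.6% with equal rings.

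**Step 5: blinding against analysis.** No arithmetic applies here. Section {17a} gives statisticians an identifier unlinked to ring. Section {20a} requires a model "accounting for clustering of participants in rings", and the Abstract and {14} require an ICC estimate. The only release of codes described is to the committee's biostatistician at interim, in {16c}. The article does not say how the other analyses obtain the ring.

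**The case against.** Four points can be made for the plan.

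- **The ring data exist.** A reader might infer from {17a} that ring membership is lost and the primary model cannot be fitted. The documents do not support that. Each participant has two identifiers, the randomization system keeps an audit trail of allocations and participant numbers, and {20a} commits to a ring-level model. A masked ring code is compatible with all of this. It follows that error rates for a primary test ignoring rings would describe an analysis nobody plans. What stands is a wording conflict.
- **Unlinking the identifier is sensible masking.** Rings are the unit of randomization, so an identifier that reveals the ring can reveal the arm. This stands for the laboratory, which has no need of ring membership. For statisticians, masking the arm and the ring's identity is enough.
- **The phrase used does not exclude a random effect.** That is true, and details of the variance are often left to an analysis plan. Even so, the article names mixed models for every treatment comparison and a different method in the next paragraph, so the plain reading is that rings are not modelled.
- **The effect is limited.** A reader might also infer that all risk-factor standard errors are too small. Step 3 shows otherwise: age, sex, co-morbidity and much exposure detail can differ between contacts in one ring. These models are also descriptive and do not estimate the drug effect. Both limits are accepted.

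**Conclusion.** The point holds in a limited form. Followed as written, the risk-factor models understate uncertainty for index-case and other ring-level factors: standard errors are about 9% too small and a 5% test has a true size of about 7.4% at ICC 0.05 and ring size 5. The range is 5.9% at ICC 0.02 to 9.8% at an assumed ICC of 0.10, with further inflation if ring sizes vary widely. Factors that vary freely within rings, the treatment comparisons and the sample size are unaffected.

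These figures assume two-sided tests, equal ring sizes and models fitted in all contacts. The ICC for symptomatic disease is not given and is taken to be the same. If correlates of symptomatic disease are examined only among infected contacts, each ring contributes about 0.15 × 5 = 0.75 people and the inflation would be smaller.

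The blinding text and the ring-based analyses conflict if read literally and must be reconciled. This is a matter of wording, not evidence that the primary analysis is impossible.

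**What to change.** 1. In {20a}, state that risk factors for transmission and correlates of symptomatic disease will be analysed by logistic mixed models with a ring random effect, or by GEE or cluster-robust errors with ring as the cluster, and with arm and site as covariates.
2. In {17a}, state that statisticians receive a masked ring code, the site and a masked arm code, and that the identifier unlinked to cluster is for the laboratory. Say that the ICC re-estimate after 60 clusters uses the same masked ring code.

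The cost is a sentence in each section, one model term and one data-management instruction. No new data are collected and the sample size does not change.
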